Concerning effectiveness, we expect that YIM will strengthen youth resilience factors, such as perceived social support and social resourcefulness (*primary outcomes*), relatedness to others, autonomy, and competence. Moreover, we expect YIM to contribute to halting or decreasing the need for (formal) support and self-reported delinquency (*secondary outcomes*). Concerning the working mechanisms of YIM, we expect that an increase in resilience factors mediates the effect of halting or decreasing the need for (formal) support and self-reported delinquency. Furthermore, the impact of YIM will be larger for some individuals than for others, based on moderators such as demographic factors, psychosocial problems, mentor-mentee relationship quality (e.g., type of support, frequency of contact, relationship duration, (non)kin), peer network quality, parental monitoring, and treatment characteristics (i.e., Halt intervention characteristics and YIM characteristics). Also, see Fig. 1 for a pictorial depiction of the theoretical model. Finally, concerning the implementation of YIM, we will explore the boosters and barriers that facilitate or prevent its successful implementation. We intend to explore boosters and barriers within three domains: the innovation domain (i.e., characteristics of the innovation being implemented: YIM), the individuals’ domain (i.e., characteristics of individuals receiving the innovation: youth and caregivers, and characteristics of individuals delivering the innovation: Halt professionals) and the inner setting domain (i.e., characteristics of the setting in which the innovation is being implemented: Halt) (Damschroder et al., 2009, 2022; Fleuren et al., 2014).

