#### Materials

Our primary outcome, with which we will assess the main intervention effect of YIM on perceived social support and social resourcefulness, will be measured with the Berlin Social Support Scales (BSSS), respectively the subscales ‘Perceived Social Support’ and ‘Support Seeking’ (Schwarzer & Schulz, 2003). All youth and caregiver(s)’ outcomes and measurement points are depicted in Table 1. In Table 2, an overview of measures administered to Halt professionals is presented.

**Table 1 Tab1:** Overview of Youth and Caregiver(s) Measurements

Concepts		Measurement	Informants	# of items	Baseline	Post-test	Follow-up
Demographic factors		Demographics	Y	18–21	*****		
Offense and referral information		Halt’s registration system	HP	-	*****		
Halt intervention characteristics		Halt’s registration system	HP	-	*****		
YIM characteristics		Halt’s registration system	HP	-		*****	
Dynamic risk factors		Halt-SI	HP	-	*****		
Psychosocial problems		Halt-SI SDQ	HP Y	- 20	***** *****		
Prosocial behaviour		SDQ	Y	5	*****	*****	*****

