**RESILIENCE FACTORS**:							
**1**	**Quality social network**:						
	1.1 Perceived social support	BSSS, *perceived social support*	Y, C	8	*****	*****	*****
	1.2 Perceived mattering	GMS	Y	5	*****	*****	*****
	1.3 Relatedness to others	BPNS, *relatedness to others*	Y	4	*****	*****	*****
	1.4 Peer network quality	IDF	Y	8	*****	*****	*****
	1.5 Mentor relationship quality	Items relational process YsoR	Y, C Y, C	11 6		*****	*****
**2**	**Social skills**:						
	2.1 Social resourcefulness	BSSS, *support seeking*	Y, C	5	*****	*****	*****
**3**	**Feelings of autonomy and competence**:						
	3.1 Competence satisfaction	BPNS, *competence*	Y	4	*****	*****	*****
	3.2 Autonomy satisfaction	BPNS, *autonomy*	Y	4	*****	*****	*****
**4**	**Attitudes towards delinquency**:		Y		*****	*****	*****
	4.1 Cognitive biases	HIT-Q, *cognitive biases subscales*	Y	39	*****	*****	*****
**5**	**Parental monitoring and family outcomes**						
	5.1 Adolescent disclosure	PMS, *AD*	Y, C	6	*****	*****	*****
	5.2 Parental solicitation 5.3 Family resilience 5.4 Parental stress	PMS, *PS* FES PSS	Y, C C C	6 14 18	***** ***** *****	***** ***** *****	***** ***** *****
**6**	**Commitment to social environment**:						
	6.1 Attachment to school	SCS, *value of school* NSCR, *school form*	Y	11	*****	*****	*****
	6.2 Structured free-time activities	IFTA and TSWF	Y	4–8	*****	*****	*****
**NEED FOR FORMAL SUPPORT**		BSSS, *need for support* IHR	Y, C	8	*****	*****	*****

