
#### Data collection and procedure

Both recruitment and data collection started on September 1st, 2022. Recruitment will stop after 15 months because researchers strive to complete pre- and post-tests within 18 months. Follow-up measurements can occur up to 24 months after the start of the data collection. Participants will be asked to fill out three questionnaires: before the initial meeting (baseline), 100 days after baseline (post-test), and nine months after baseline (follow-up). After giving consent via the flyer, participants will automatically be referred to the first online questionnaire and instructed to complete it before their initial meeting at Halt. After that, researchers will approach eligible participants for post-test and follow-up measurements (see Fig. 2). All questionnaires will be administered in Dutch and will take approximately 30 min to complete. Participants will receive €7,50 per completed questionnaire; when they complete all questionnaires, they may win AirPods (€130).

Complementary to the questionnaires, we will receive pseudonymised youth case data from Halt’s registration system. Professionals in both conditions will register the characteristics of the Halt intervention (e.g., number of meetings, type of crime) and the risk assessment (i.e., Halt-SI) per youth case. In the CAU plus YIM condition, professionals will additionally register characteristics of YIM (e.g., the reaction of youth to YIM, caregivers’ approval of YIM, and the youth’s relation to the YIM (e.g., uncle, grandmother)). Most importantly, professionals will report the steps they have taken to implement YIM: (1) the YIM question was asked (“Who, an adult aside from your caregiver(s), can you turn to if necessary?”), (2) steps were taken to support youth in identifying and nominating a YIM, such as the network or YIM assignment, and (3) a YIM was positioned in an official meeting with all parties. Note that the third level of implementation is only possible if youths can identify and nominate a mentor.

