#### Data analyses

First, for both the effect analyses on the different outcome variables and moderator and mediator analyses, we will perform multiple regression analyses with baseline levels of the outcome variable as a covariate and condition as a predictor variable. Second, to correct for the clustering of participants within regions and within Halt professionals, the regression analyses will be performed in a multilevel model with the participant as level 1, the professional as level 2, and the region as level 3 cluster variables. Third, to correct for multiple testing, we will implement a Benjamini Hochberg False Detection Rate (FDR; (Benjamini & Hochberg, 1995) correction on the p-values for the respective outcome tests. Fourth, to test for the similarity between conditions, we will compare the two groups of Halt professionals and both conditions on several characteristics (e.g., demographic factors, professionals’ educational level, or youths’ psychological problems). If differences are detected between conditions, we will use propensity score matching (PSM) techniques (Caliendo & Kopeinig, 2008) to match participants in the CAU plus YIM condition to participants in the CAU condition. Lastly, we will implement the Intention-to-Treat (ITT) principle for handling missing data on post-test and follow-up measurements (Detry & Lewis, 2014; Yeatts & Martin, 2015). Thus, we will analyse all missing data of participants according to their assigned condition, regardless of whether the intervention was received or completed (Detry & Lewis, 2014; Yeatts & Martin, 2015). Missing data points will be estimated by performing Full Information Maximum Likelihood (FIML) methods. We will consider the percentage of missing data and patterns of missing data (e.g., missing completely at random) (Bennett, 2001; Schulz & Grimes, 2002).

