It is also crucial to mention three potential challenges. First, allocating youths to either condition (i.e., to a non-YIM-trained or YIM-trained professional) is non-random. Random allocation is impossible because Halt’s distribution office considers professionals’ workload. This might lead to an unequal division of youth cases over conditions and, thus, less comparable conditions. Differences between conditions could then possibly be explained by confounding factors instead of the effects of YIM, such as differences in the severity of the youth case (Flannelly et al., 2018). To ensure comparable conditions, we will match professionals in the CAU plus YIM condition within each region to professionals in the CAU condition. Nevertheless, we must be cautious of drawing causal inferences. We will also address other confounding factors between conditions, such as differences in the number of sessions or types of activities. Second, baseline and post-test measurements will occur without the knowledge of the implementation level of YIM in the CAU plus YIM condition. We will assess three levels of implementation steps taken by a professional: (1) the YIM question was asked, (2) steps were taken to support youth in identifying and nominating a YIM, and (3) a YIM was positioned in an official meeting. External factors can influence these steps, such as a youth not being able to identify or nominate a YIM. If this is the case, it is impossible to position a YIM. We will, however, instruct professionals to explain and motivate YIM in all youth cases, possibly leading to the positioning of a YIM. Overall, we expect that all cases will at least have the second level of implementation. However, due to the natural course of YIM, we cannot rule out natural variation in the level of implementation. Because this might impact the findings, we will consider these implementation levels in our analyses. Moreover, these implementation levels will allow us to explore whether different elements of YIM affect the approach’s effectiveness. Third, all participants will voluntarily sign up for the study, potentially leading to a selective pool of more intrinsically motivated participants. Even though Halt has a broad population, with varying degrees of problems and different types and severity of offences and crimes, the registered group might not entirely represent the Halt population. Potentially, youth with more severe problems might be missed. This would, however, apply to both conditions – if this were to be the case. Hence, to appeal to the entire population at Halt, we will offer a monetary contribution per completed questionnaire and the chance to win the grand prize, namely AirPods. Fourth, a challenge in the focus group interviews is that being in a group, people might not feel comfortable enough to share their true perspectives and opinions on working with the innovation. Moreover, some individuals could be more dominant in the conversation than others, which might discourage some individuals from actively participating. To encourage active participation and a comfortable environment, we will perform *think-pair-share* techniques (Kagan, 1994; Lyman, 1981) in a neutral environment without the involvement of YIM and Halt management.

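### YIM characteristics and mentor relationship quality are named as moderators of YIM's impact, but one exists in a single arm and the other only after treatment, so the stated model cannot show effect modification by either

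*Protocol article*

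**What the plan says.** The present study section says that YIM's impact will be larger for some youths than for others and names the moderators. Besides demographic factors and psychosocial problems, these are "mentor-mentee relationship quality (e.g., type of support, frequency of contact, relationship duration, (non)kin" and then "peer network quality, parental monitoring, and treatment characteristics (i.e., Halt intervention characteristics and YIM characteristics". The same section makes an increase in resilience factors the mediator of the effects on need for formal support and on delinquency.

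The Data analyses section of Study 1 covers effect, moderator and mediator analyses together: "we will perform multiple regression analyses with baseline levels of the outcome variable as a covariate and condition as a predictor variable". Professional and region are added as cluster levels.

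On measurement:

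- The Data collection and procedure section states: "In the CAU plus YIM condition, professionals will additionally register characteristics of YIM". Table 1 marks the row "YIM characteristics" at post-test only.
- Table 1 marks the row "1.5 Mentor relationship quality" at post-test and follow-up, with the baseline cell empty. The row stands under resilience factors.
- Table 1 marks peer network quality, adolescent disclosure and parental solicitation at all three time points.
- Table 1 marks Halt intervention characteristics as baseline. The Conditions section, however, has the professional settle content and duration during the initial meeting, and says that YIM, if selected, takes the place of other Halt activities.

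The Discussion adds that "these implementation levels will allow us to explore whether different elements of YIM affect" the approach's effectiveness.

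**The concern.** Asking for whom YIM works means asking how the difference between CAU plus YIM and CAU changes with some feature of the youth. That requires a feature which has a value in both arms and which the intervention has not altered. YIM characteristics fail the first requirement and mentor relationship quality fails the second. Mentor relationship quality also cannot enter the stated model as an outcome, or be scored as an increase from baseline for mediation, because no baseline is collected.

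At stake is one of the trial's three main questions. The Discussion intends the answer to guide which youths are offered YIM. A pattern seen among YIM youths alone, for example better outcomes with a certain type of mentor, could be read as showing who benefits from YIM when it may only show who would have done well anyway.

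**Working it through.** There is no stated figure to reproduce; the check is structural.

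**Step 1: sort the named moderators by arm and timing.** Baseline is the questionnaire completed before the initial meeting. Post-test is 100 days later, and both programmes aim to finish within 100 days.

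| Moderator | In both arms? | Before treatment? |
|---|---|---|
| Demographic factors | yes | yes |
| Psychosocial problems (SDQ) | yes | yes |
| Peer network quality | yes | yes |
| Parental monitoring (disclosure, solicitation) | yes | yes |
| Halt intervention characteristics | yes | no: set at the initial meeting |
| Mentor relationship quality | not stated | no: post-test and follow-up |
| YIM characteristics | no: CAU plus YIM only | no: post-test |

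Four of the seven are sound, two are not, and one is doubtful.

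**Step 2: identification for YIM characteristics.** The article writes out no interaction term. The usual reading of a moderator analysis with condition as predictor is

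E[Y] = b0 + b1·Y0 + b2·C + b3·M + b4·C·M,

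where Y0 is the baseline outcome, C is condition (0 = CAU, 1 = CAU plus YIM) and M is the moderator. The rank of this five-column matrix was computed with 150 youths per arm, the planned number:

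- M absent in CAU, complete cases: C = 1 in every row, so C equals the intercept and C·M equals M. Three distinct columns remain (1, Y0, M): rank 3 of 5.
- M coded 0 in CAU: C·M = M in every row. Four distinct columns remain: rank 4 of 5.
- M measured at baseline in both arms: rank 5 of 5.

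In the first two cases b4 cannot be separated from b3, whatever the sample size. Random effects for professional and region do not change this. Full Information Maximum Likelihood does not help either: the CAU values are not lost but undefined, and the data hold nothing on how M relates to outcome in CAU.

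**Step 3: mentor relationship quality.**

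- As a moderator: YIM exists to establish and support this relationship, and the measure is taken when the programme is due to be over. Condition can therefore shift it. Youths with equal values in the two arms are then not like for like, and adjusting for the measure can absorb part of the effect under study.
- As an outcome: the model requires Y0, which does not exist.
- As a mediator: the hypothesis concerns an increase. The only change available runs from post-test to follow-up, after the programme.

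**Step 4: Halt intervention characteristics.** The professional, who differs by arm, sets them after allocation, and YIM displaces other activities. This is the weaker case, because the article expects the same number of youth-professional meetings in both arms. The mix of activities is the affected part.

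**The case against.** The strongest reply is that the article never writes a condition-by-moderator term. How each moderator enters the model, and at which time point, is detail that a condensed article may leave to a fuller plan. A within-arm analysis of YIM characteristics can be estimated. So can the four-column version above, for example comparing CAU with youths who have a kin mentor and with youths who have a non-kin mentor.

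Part of this stands. The interaction is inferred, and the variables can be analysed in some form. But those analyses answer another question. The within-arm slope shows how outcome varies with the characteristic among YIM youths. It equals effect modification only if the same youths' outcomes under CAU would not have varied with it, and the trial cannot observe that. Nor is this merely absent detail: the article calls these variables moderators of YIM's impact, gives one model, and records measurement times that do not fit it. No within-arm restriction is stated.

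Several stronger readings are tempting but unsupported:

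- A reader might think peer network quality and parental monitoring are equally flawed, since they are also resilience factors. They have baseline values, and a baseline level can moderate while change mediates.
- A reader might take mentor relationship quality to exist only in the YIM arm. Table 1 names youths and caregivers as informants, with no arm restriction.
- A reader might infer a planned comparison of each implementation level with CAU that would favour YIM. No such contrast is stated. The Discussion speaks of exploring, and itself notes that a youth who cannot nominate a mentor cannot reach the third level.

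**Conclusion.** The point holds for two named moderators and, more weakly, for a third. Effect modification by YIM characteristics is not identified; this follows from the measurement plan and needs no numerical assumption beyond reading moderator in its usual sense. Mentor relationship quality is a post-treatment variable as a moderator, and it has no baseline for the outcome or mediator models. Halt intervention characteristics are set after allocation and partly changed by YIM.

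No bias size can be given. It would depend on how strongly these variables are tied to condition and outcome, and the article offers no figures for that.

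A reader might conclude that the question of for whom YIM works cannot be answered at all. That goes too far: four of the seven named moderators are usable as measured. The primary outcomes and the comparison by assigned condition are unaffected. The correction is worth making because it is cheap and protects a stated main question.

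**What to change.** For the question of for whom YIM works, restrict moderators to variables measured before the initial meeting in both arms: demographics, SDQ scores, offence information, and the baseline values of peer network quality, adolescent disclosure and parental solicitation. Name baseline as the time point for each.

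Report YIM characteristics, mentor relationship quality and implementation level as within-arm, associational analyses adjusted for baseline social support. Make no claim of effect modification or of a causal effect of level. Exclude mentor relationship quality from the baseline-adjusted outcome models and from the mediator models. Do not present Halt intervention characteristics as pre-treatment moderators.

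A complier-average analysis of implementation level is not a way round this. Youths below the third level still receive parts of YIM, and allocation is not random.

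The change is one of analysis wording and needs no new data. The cost is fewer moderator claims.

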**Fig. 1 Fig1:**
[figure not shown]
Theoretical model of YIM: outcomes, mediators, and moderators

## Methods and design

### Aims and setting

Our main aim is to examine whether YIM strengthens resilience factors, such as perceived social support and social resourcefulness, in delinquent youth. To do so, we will study YIM at Halt, a Dutch juvenile justice system organisation which offers youths a diversion program subsidised by the Ministry of Justice and Security. In the Netherlands, all juvenile offenders (12 to 18 years) are referred to Halt after committing relatively minor offences or crimes (Wolthuis & Stentoumi, 2023). Common offences and crimes include public intoxication, extreme school absenteeism, shoplifting and vandalism. Halt has the nationwide task of providing these youths with a tailored intervention aimed at preventing reoffending and increasing future opportunities (Halt, n.d.). Mainly, Halt works with first- and second-time offenders who remain in the community. Working with 15,000 youths yearly, Halt has a unique position to identify youths (and families) in vulnerable circumstances. These youths are guided towards the necessary formal support systems, such as youth care organisations or addiction treatment centres. Since 2019, 36 Halt professionals (15% of all Halt professionals) have been trained in YIM, allowing YIM-trained professionals to strengthen the informal support system by involving a non-parental adult from the youth’s social network. The Halt program is implemented throughout the Netherlands, but the organisation is organised into four central regions: (1) North-Holland-Centre, (2) North-East, (3) South, and (4) West. Each region has sub-teams supervised by a region manager, and within each region, multiple professionals have been trained in YIM. Of all YIM-trained professionals, 31 (86%) have agreed to collaborate with the YIM-Halt trial. More details on the content of the Halt intervention can be found under “Conditions” > “Care as Usual (CAU) condition”. The quasi-experimental trial (Study 1) and the qualitative study (Study 2) will be performed at Halt and are presented below.

### Study 1: quasi-experimental trial

#### Design

In this quasi-experimental design, youth referred to Halt are non-randomly allocated to either a non-YIM-trained Halt professional implementing *Care as Usual* (CAU; *N*_*professionals*_ = 31) or a YIM-trained Halt professional implementing *CAU plus YIM* (*N*_*professionals*_ = 31). Even though Halt’s distribution office allocates youth cases to professionals independent of case type and severity, they consider professionals’ workload within each region. This could lead to unequal distribution of youth cases over conditions. To ensure comparable conditions, the two groups of professionals are matched on educational level and region. Thus, despite non-random allocation, we expect similar conditions regarding (1) professionals’ characteristics and (2) case type and severity. Adolescents are our primary informants, but caregiver(s) of youths are also approached. This trial is registered at Clinicaltrials.gov (NCT05555472).

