**REOFFENDING**							
	Self-reported delinquency Youth delinquent behaviour	AHSRD CBCL, *delinquent behaviour*	Y C	17 13	*****	*****	*****

*Note Informants*. *HP* Halt professionals; *C* Caregiver(s); *Y* Youths

*Note Questionnaires. **AD* Adolescent Disclosure; *AHSRD* Add Health Self-Reported Delinquency; *BPNS* Basic Psychological Needs Scale; *BSSS* Berlin Social Support Scale; *CBCL* Child Behaviour Check List; *FES* Family Empowerment Scales; *GMS* General Mattering Scale; *Halt-SI* Risk Assessment Tool Halt; *HIT-Q* How I Think Questionnaire; *IDF* Items Delinquent Friends (Van der Laan & Blom, 2006); *IFTA* and *TSWF * Items Free-Time Activities and Time Spent With Friends (Van der Laan & Blom, 2006); *IHR *Items Halt Research (Ferwerda, 2006); *PMS* Parental Monitoring Scales; *PPI* Peer Pressure Inventory; *PS* Parental Solicitation; *PSS* Parental Stress Scale; *NSCR* Netherlands Institute for the Study of Crime and Law Enforcement; *SCS* School Connectedness Scale; *SDQ* Strength and Difficulties Questionnaire; *WODC* Research and Documentation Centre in the Netherlands; *YsoR* Youth Strength of Relationship; *YSR* Youth Self Report

**Table 2 Tab2:** Overview of Halt Professional Measurements

Concepts	Measurement	Informant	# of items	Before recruitment
Demographic factors	Questionnaire	HP	4	*****
Educational level	Questionnaire	HP	4	*****
Work experience	Questionnaire	HP	2	*****
Outcome Expectancy	OES	HP	3	*****
Personality	QBF	HP	30	*****

*Note Informants. **HP* Halt professionals

*Note Questionnaires. **OES* Outcome Expectancy Scales; *QBF* Quick Big Five

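### Professionals are matched only on education and region, and no stated analysis step adjusts for their other characteristics, so confounding by professional may remain in the YIM effect

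*Protocol article*

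**What the plan says.** All of this is in the protocol article.

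- **Who carries the condition.** Under Aims and setting, "36 Halt professionals (15% of all Halt professionals) have been trained in YIM", and "Of all YIM-trained professionals, 31 (86%) have agreed to collaborate with the YIM-Halt trial". Under Design, these 31 deliver CAU plus YIM and 31 untrained colleagues deliver CAU, so each professional is in one condition only.
- **How professionals are made comparable.** Under Design, "the two groups of professionals are matched on educational level and region". The inference drawn is that "despite non-random allocation, we expect similar conditions regarding (1) professionals’ characteristics and (2) case type and severity". The Discussion mentions region only: "we will match professionals in the CAU plus YIM condition within each region to professionals in the CAU condition".
- **What is measured on professionals.** Table 2 ("Overview of Halt Professional Measurements") lists demographics, educational level, work experience, outcome expectancy and personality, all taken before recruitment.
- **The model.** Study 1, Data analyses gives a regression with the baseline outcome as covariate and condition as predictor, with participant, professional and region as levels. No professional characteristic is named as a covariate.
- **The check and remedy.** The same section says "we will compare the two groups of Halt professionals and both conditions on several characteristics". If the conditions differ, propensity score matching is used "to match participants in the CAU plus YIM condition to participants in the CAU condition". The variables in the score are not listed.
- **Caution.** The Discussion warns about causal inference and promises to address other confounders. It gives number of sessions and types of activities as examples and names no method.

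**The concern.** Matching on two factors makes the groups alike on those two factors. It gives no ground for expecting similarity in experience, personality or anything else that affects how a youth fares with a professional.

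Condition does not vary within a professional, so any difference in mean professional effect between the two groups adds directly to the condition coefficient. The random intercept for professional corrects the standard error for clustering. It assumes that professional effects are unrelated to condition, so it cannot separate such a difference from the effect of YIM.

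The remedy is aimed at participants. All youths of one professional share that professional's traits, so pairing youths on youth characteristics alone leaves an imbalance between professionals in place. The remedy also starts only once a difference has been detected, and with 31 per group detection is weak. At stake is whether a small positive estimate reflects YIM or the professionals who deliver it.

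**Working it through.** The plan states no figure on this point, so there is none to reproduce. The calculations below are illustrative.

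**Inputs from the article:** 31 professionals per group; 300 youths; reference effect d = 0.21 (Power Analysis), used only as a yardstick.

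**Assumed, because the article does not give them:** professional ICC 0.02 to 0.10 (centre 0.05); correlation r of 0.3 to 0.7 between a trait and the professional's effect on outcome; imbalance s = 0.5 SD in that trait; detection by a two-sided t-test at 0.05.

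**1. Would the similarity check find the imbalance?**
SE of a standardised difference = √(2/31) = 0.254. Noncentral t, 60 df, noncentrality s × √(31/2):

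| True imbalance (SD) | Power |
|---|---|
| 0.2 | 12% |
| 0.3 | 21% |
| 0.5 | 49% |
| 0.8 | 87% |

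**2. How large could the bias be?**
With a total outcome SD of 1, professional effects have SD √ICC. One SD of the trait moves the professional effect by r × √ICC, so bias = s × r × √ICC. For s = 0.5:

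| ICC | r = 0.3 | r = 0.5 | r = 0.7 |
|---|---|---|---|
| 0.02 | 0.021 (10%) | 0.035 (17%) | 0.049 (24%) |
| 0.05 | 0.034 (16%) | 0.056 (27%) | 0.078 (37%) |
| 0.10 | 0.047 (23%) | 0.079 (38%) | 0.111 (53%) |

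Percentages are of d = 0.21. The sign is as likely negative as positive, since the article does not say which group has more of any trait.

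**3. What does level-2 adjustment do?**
Simulation of professional means: 62 professionals, 4 youths each (300 × 0.8 / 62 = 3.9 after 20% drop-out), ICC 0.05, r = 0.5, s = 0.5, no true YIM effect. Any covariate beyond the first is pure noise.

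| Level-2 covariates | Bias | SD of estimate | Root mean squared error |
|---|---|---|---|
| none | 0.056 | 0.136 | 0.147 |
| 1 (the confounder) | 0.00 | 0.139 | 0.139 |
| 3 | 0.00 | 0.141 | 0.141 |
| 11 | 0.00 | 0.152 | 0.152 |

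The unadjusted row follows by hand: SD = √[(2/31) × (0.05 + 0.95/4)] = 0.136, and √(0.056² + 0.136²) = 0.147. The adjusted bias is zero by construction, because the covariate entered is the confounder. What the table shows is the price: one to three covariates cost little, while about eleven (close to all of Table 2) bring the total error above that of the biased, unadjusted estimate.

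**The case against.** The strongest reply is that the article does not restrict the remedy as much as it may seem. Its similarity check covers professionals and gives their educational level as an example. The propensity covariates are unlisted, and a participant-level score can include the professional's experience or personality; youths would then be paired across similar professionals. The Discussion also promises to address further confounders and advises causal caution. A full covariate list is commonly left to an analysis plan that is not shown here.

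Much of this stands. A reader might infer that matching youths is the only remedy, that it cannot work, and that the confounding therefore stays in the estimate. The documents do not support that, because nothing excludes professional traits from the score. Nor do they support the inference that professionals chose to be trained. The article says how many were trained and how many agreed to join the study, but not how staff were selected for training.

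The reply does not remove the point. The article does not leave confounding to another document: it states a model, a trigger, a remedy and an expectation of similarity. None of these assigns a use to professional traits beyond the comparison. The further promise names no method, and its examples are not traits of professionals. Even a score that included such traits would be used only if a difference were detected.

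The figures are also open to challenge. They rest on assumed values, the article names no test for the similarity check, and d = 0.21 comes from formal mentoring and delinquency, not from the social support scales that are primary here. In the centre case the bias (0.056) is well below the standard error (0.136).

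**Conclusion.** The point holds as a risk that the stated analysis does not control. Beyond educational level and region, no stated step adjusts for differences between the two groups of professionals, and the similarity expected of them goes further than the matching supports. Confounding may remain. The documents do not show that it exists, in which direction it runs, or how large it is.

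If the trigger is a two-sided 5% test, a 0.5 SD imbalance goes undetected about half the time. The resulting bias is illustratively 0.03 to 0.08 SD at an ICC of 0.05 (0.02 to 0.11 over ICC 0.02 to 0.10). That is not negligible beside the small effect the article uses for planning. The case for changing the plan rests on the structure of the design and on the fact that the covariates are already being collected, not on a particular value in that range.

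**What to change.** In Study 1, Data analyses:

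1. Prespecify about one to three Table 2 characteristics that YIM training cannot change, for example work experience, as level-2 covariates in every effect model, whatever the similarity check shows.
2. If propensity score matching is used, put the same variables in the score and say so.
3. Leave outcome expectancy out of the adjustment and report it descriptively. It is measured in staff who are already trained and may be a result of the training.

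Under Design, limit the expected similarity of professionals to educational level and region.

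The cost is wording plus a small loss of precision: the SD of the estimate rises from about 0.136 to 0.139–0.141 with one to three covariates. The list should stay short, because entering all of Table 2 could lose more in precision than it gains in bias. Adjustment covers measured traits only, so the Discussion's causal caution should stay.
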